## ***z. 8.7 Data and Safety monitoring***

A DSMB will not be established as the outcome will be determined through a cross-sectional survey at the end of the intervention. A TSC will be established which will include a mix of senior trial investigators including the PI and external members, with an independent chair. The TSC will review operational performance including uptake, retention and adverse events on an ongoing basis, and will advise the study team on trial conduct. Data on the uptake of each component of the trial intervention will be captured electronically in all intervention communities. We will monitor intervention uptake on a monthly basis. This will be used to inform adaptations to improve uptake of and access to the intervention.

Adverse events, defined as an untoward medical occurrence in an individual to whom a medicinal product has been administered including occurrences that are not necessarily caused by or related to that product, among individuals accessing the intervention will be recorded. The products referred to include ART, STI treatment, contraception and MHM products.

Social harms are defined as any untoward social occurrences that happen to a participant as a result of their participation in the study, with examples including loss of employment, harassment by neighbours, shunned by family, rejection by partner etc. Because this study is a community-randomized trial of a multi-faceted intervention, the majority of people in the community affected by the implementation of the study will not be participants in the evaluation surveys, and so the definition of social harm for this study will be expanded to also include any untoward social occurrences that happen to a community, or groups or individuals within a community, as a result of implementation of the study intervention. Social harms will be monitored throughout the study (through report from those accessing the CHIEDZA intervention) and study staff will be trained to report these on a regular basis and to provide appropriate counselling and/or referral to appropriate resources, as needed. Staff may also become aware of social harms passively e.g. if they live in the intervention communities, and will be encouraged to report these.

Discussion of social harms will be addressed with the TSC and with the YAG. The qualitative research to be conducted as part of the process evaluation will also explore social harms in the community. The study team will review the social harms reports monthly, or sooner, if a concerning trend or event is identified. If the team judges an individual social harm, or a trend in social harms, to be serious or unexpected, they will work together with appropriate bodies (IRBs, YAG, TSC, Trial sponsor) to determine if a response is indicated, and if so, what it should be.

Adverse events and social harms will be reported to the ethics committees according to their individual requirements.

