Partner notification is integral to effective STI care to reduce infection rates in the population and to prevent both re-infection and the consequences of untreated infections. There are a number of approaches to partner notification, including patient referral (whereby patients are encouraged to contact their sex partners themselves), provider referral (the health care provider notifies the partner and arranges treatment), contractual patient-provider referral (a two-step approach that links patient and provider referral methods), and expedited partner therapy (the diagnosed patient takes the prescriptions or medication to his/her partner)". However, the evidence is not present to identify a single optimal partner notification strategy for a particular STI. Despite the importance of partner notification, it is often not performed adequately. There are a number of potential reasons for this, including concerns about adverse partner reactions, such as risk of violence or of the partner leaving. Embarrassment and stigma are also reported as perceived barriers to partner notification and partner notification is also lower in casual relationships.

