## ***r. 6.2 Outcome data from cross-sectional survey***

The cross-sectional survey will be conducted at community level by trained research assistants, using electronic tablets with pre-designed data entry forms including validation checks and skip patterns. Fingerprints will be collected from each survey participant. The research assistants will ask questions and fill in answers on the tablet. For sensitive questions, the participant will input the answers directly to prevent social desirability bias. Biometric records obtained from participants in the cross-sectional survey will be matched against all biometric records of clients accessing the intervention to assess degree of contamination and coverage of the intervention.

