***cc. 9.1 Cross-sectional survey tests***

Participants will be asked to provide a blood sample for anonymised HIV testing ( a dried blood spot specimen). The samples will be assayed in batches for HIV antibodies using an ELISA 4th generation HIV antibody assay. All positive tests will be confirmed with a separate ELISA assay (assay to be determined) on the same sample. One in twenty samples that test HIV negative will also be re-tested to provide Quality Assurance. All HIV-positive samples will be tested for HIV VL. The assay to be used will depend on local availability. In addition to the tests described above, study participants will be asked to provide written informed consent for their specimens to be stored for possible additional, future testing (long-term storage). The specimens of participants who do not consent to long-term storage for future research will be destroyed after all protocol-related testing has been completed. Specimens will only bear the study ID of the participants. The study ID number will be put on each specimen for anonymised testing.

All participants will be provided with information about HIV testing and counselling and where this can be accessed. Those who wish to know their HIV status will be referred to the local health facility for expedited diagnostic HIV testing. Home-based testing is not being offered based on previously low levels of uptake due to concerns by youth of unintended disclosure and lack of complete privacy when HIV testing is performed at home.

Participants who are randomised for STI testing and have a positive STI test result will be contacted (using a prior agreed pseudonym) and will be treated by the study team and partner notification using client referral undertaken.

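### Section 8.7 records adverse events only in people using the intervention service, but section 9.1 has the study team treat STI-positive survey participants in both arms

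*Combined protocol and SAP*

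**What the plan says.** Section 8.7 (Data and Safety monitoring) defines an adverse event broadly, as any untoward medical event in a person given a medicinal product, whether or not the product caused it. It then limits who is covered: adverse events "among individuals accessing the intervention will be recorded". On scope it adds: "The products referred to include ART, STI treatment, contraception and MHM products".

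The same section defines social harm as an untoward social event that befalls a participant because of taking part. It widens this to communities, groups and individuals affected by the implementation of the intervention. On collection it says: "Social harms will be monitored throughout the study (through report from those accessing the CHIEDZA intervention". The sentence goes on to say that study staff will be trained to report such harms regularly. A further route follows: "Staff may also become aware of social harms passively e.g. if they live in the intervention communities, and will be encouraged to report these".

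Section 9.1 (Cross-sectional survey tests) says that survey participants selected for STI testing who test positive will be contacted and "will be treated by the study team and partner notification using client referral undertaken". It names no arm. The STI survey covers all 16 clusters in Harare and Bulawayo, intervention and control alike.

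Section 8.4.2 lists the risks of the endline survey: loss of privacy, discomfort from blood sampling, and distress from questions. It mentions neither the STI treatment nor the partner notification. Section 8.5.3 gives survey participants contact details for the study team and the ethics body, for complaints or issues.

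**The concern.** A survey participant treated by the study team meets the definition of a person in whom an adverse event can occur, and STI treatment is a named product. Someone who has never used the CHIEDZA service is nevertheless outside the population in whom events are recorded. That describes nearly everyone treated in control clusters and some of those treated in intervention clusters. If the protocol is followed as written, a reaction to study-given treatment in such a person need not be recorded, and so need not reach the Trial Steering Committee or the ethics committees.

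Social harms raise a related, weaker point. Survey participants in both arms fall within the definition, but the main active route is report from service users. Partner notification makes this relevant: section 5.5.1, in its general background, gives "concerns about adverse partner reactions, such as risk of violence or of the partner leaving" among the reasons why notification is often not carried out.

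**Working it through.** **1. Do the two sections meet anywhere?**

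- Product in scope: STI treatment (8.7).
- Recording population: users of the intervention (8.7).
- People given the product by the study: service users, and STI-positive survey participants with no limit to one arm (9.1).
- Bridging text: none found. Section 8.7 sends adverse events and social harms to the ethics committees under their own requirements, but does not widen who is observed. Section 8.8 says that STI treatment follows national guidelines, which concerns the treatment and not the recording.

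**2. Inputs for the size**

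- 300 survey participants per cluster for STI outcomes (5.5.3, Table 8).
- 16 clusters (Executive Summary, Table 8). I take 8 per arm, from 1:1 allocation within strata and the Figure 2 note of 4 intervention and 4 control clusters per survey round.
- STI prevalence of 17% in the control arm (Table 8).

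**3. Reproducing Table 8 first.** I used the Hayes–Bennett formula for unmatched clusters,

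c = 1 + (z₁ + z₂)² × [p₁(1−p₁)/m + p₂(1−p₂)/m + k²(p₁² + p₂²)] / (p₁ − p₂)²,

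with c = 8 per arm, m = 300, p₁ = 0.17 and two-sided 5% significance (my assumption, as the level is not stated), solved for p₂:

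| Power | k | Table 8 | Recomputed |
|---|---|---|---|
| 80% | 0.25 | 11% | 10.9% |
| 80% | 0.3 | 10% | 10.1% |
| 90% | 0.25 | 10% | 10.1% |
| 90% | 0.3 | 9% | 9.2% |

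The table reproduces, so 8 clusters per arm and 300 per cluster are the right reading of it.

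**4. Expected positives**

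- Control clusters: 8 × 300 × 0.17 = 408.
- Intervention clusters: 8 × 300 × 0.09 = 216 to 8 × 300 × 0.11 = 264 at the prevalences in Table 8, or 408 if there is no effect. Table 8's 9% to 11% are detectable limits, not forecasts.

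**5. Who is outside the rule**

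- Control clusters: about 408, less any who crossed over and used the service.
- Intervention clusters: (positives) × (1 − a), where a is the share who had attended CHIEDZA. The documents give no value for a. The survey is designed to measure it by fingerprint matching (5.1).

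**6. Plausibility of full recruitment.** The plan implies 16 × 300 = 4,800 participants. Supplementary Table 1 shows 2,885 + 2,716 = 5,601 analysed, so full recruitment is not an optimistic assumption overall. That table is not split by arm, so I keep to the planned 300 per cluster.

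**The case against.** The strongest reply is that safety monitoring is wider than section 8.7's main sentences suggest. Much of this stands, and it limits the point.

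- A reader might infer that social-harm capture is confined to service users. It is not. Staff are trained to report harms and encouraged to pass on what they hear (8.7). The qualitative work explores harms in the community (8.7), and the process evaluation is meant to measure them (8.4.1). Community engagement gathers feedback on them (4.3), and survey participants in both arms hold contact details (8.5.3). These routes are mostly passive or unquantified, and where 8.7 and 4.3 name a place it is the intervention communities. Section 5.2.4, however, does not confine the community-member interviews to intervention clusters.
- A reader might infer that harms can never be compared between arms. The documents show only that no such comparison is planned. Harm from implementing the intervention has no control-arm counterpart by definition.
- A reader might infer that attendee reports have no denominator. Visits and services are recorded by client (6.1.2), and uptake is reviewed monthly (8.7).
- A reader might want a social-harm block in the endline questionnaire, since that survey already allows private entry: "For sensitive questions, the participant will input the answers directly to prevent social desirability bias". Such a block would measure harm from all causes, not harm from the study. It would also come before the survey's own STI treatment and so could not capture its consequences. The referral pathways for partner violence are described only as part of the intervention service (3.2.4). Whether to add it is a debatable trade-off, not the repair of an error.
- The partner-reaction text in 5.5.1 is background on why notification often fails. It does not assess this survey's procedure.

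It can also be said that operating procedures, which are not public, may already cover treated survey participants. That is possible, but the protocol states a restrictive rule, and a procedure that went further would be at odds with it. None of these replies reaches the conflict between 8.7 and 9.1 on adverse events.

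**Conclusion.** The point holds for adverse events: sections 8.7 and 9.1 are inconsistent and must be reconciled. About 408 control-cluster participants are clearly outside the recording rule, apart from any who used the service. Intervention-cluster positives who never attended add to this by an unknown number.

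The 408 rests on four assumptions: 8 control clusters, 300 recruited in each, every positive reached and treated, and the 17% being the share of people whose result leads to treatment. Table 8 does not say which of the five organisms tested the 17% covers, so the true number could be higher or lower.

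A reader might add both arms together and put 624 to 816 people outside capture (408 + 216 to 408 + 408). The documents do not support that, because intervention-cluster participants who attended CHIEDZA fall within section 8.7.

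For social harms the supported statement is narrower. The definition covers every study participant, while the main active route is report from service users. The primary endpoint and the efficacy analyses are not affected.

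**What to change.** In section 8.7, change the recording population to: people using the intervention service, and survey participants whom the study team treats or asks to notify a partner. State that adverse events and social harms in the added group are recorded when reported at the contacts the team already makes under section 9.1, or through the contact details on the consent form (8.5.3). Cross-refer sections 8.7 and 9.1 so that the two agree. Nothing about the treatment itself needs to change.

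The cost is a protocol wording change and a little more recording. The limit is that section 9.1 describes no contact after treatment and notification, so events after the last contact would be captured only if the participant reports them.

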## ***aa. 8.8 Clinical management during and post-study***

HIV treatment in the intervention arm will be provided according to national guidelines which stipulate that all individuals who test HIV-positive are eligible

for ART regardless of age or disease stage. ART will be obtained through the national health systems and documentation of individuals will be done in line with existing procedures in the public sector. Procedures for ensuring that individuals with HIV starting treatment are registered within the national system and referral criteria and pathways for those requiring health-facility-based care will be established (e.g. those who have incident symptoms or side-effects). Other clinical management e.g. treatment for STIs and provision of contraception will also follow national guidelines.

CAPS groups will be trained and supported to become self-sustaining over the intervention period, so that following the intervention period the groups will be maintained. Individuals accessing ART through the CHIEDZA intervention will be made aware that following the end of the intervention period they will have the option of continuing to be part of a CAPS group (should the group agree) or to access ART from their nearest PHC.

### ***bb. 8.9 Ethical Review***

Approval to conduct this study will be obtained from the MRCZ, the BRTI IRB and the LSHTM Ethics Committee. Where there is disagreement or discordant IRB requirements the condition providing the highest level of human subject protection will be implemented. Adverse events will be reported on a regular basis according to the individual requirements of these IRBs, and annual reports will be sent to ethics committees according to the requirement of each committee.

- **9. Laboratory Procedures**

Testing of specimens will be performed at accredited laboratories that will adhere to GCLP and with quality management systems in place, with regular external audit of laboratory procedures. All activities related to processing, labelling of samples, testing, storage and shipment (if required) will follow Standard Operating Procedures.

***cc. 9.1 Cross-sectional survey tests***

Participants will be asked to provide a blood sample for anonymised HIV testing ( a dried blood spot specimen). The samples will be assayed in batches for HIV antibodies using an ELISA 4th generation HIV antibody assay. All positive tests will be confirmed with a separate ELISA assay (assay to be determined) on the same sample. One in twenty samples that test HIV negative will also be re-tested to provide Quality Assurance. All HIV-positive samples will be tested for HIV VL. The assay to be used will depend on local availability. In addition to the tests described above, study participants will be asked to provide written informed consent for their specimens to be stored for possible additional, future testing (long-term storage). The specimens of participants who do not consent to long-term storage for future research will be destroyed after all protocol-related testing has been completed. Specimens will only bear the study ID of the participants. The study ID number will be put on each specimen for anonymised testing.

All participants will be provided with information about HIV testing and counselling and where this can be accessed. Those who wish to know their HIV status will be referred to the local health facility for expedited diagnostic HIV testing. Home-based testing is not being offered based on previously low levels of uptake due to concerns by youth of unintended disclosure and lack of complete privacy when HIV testing is performed at home.

Participants who are randomised for STI testing and have a positive STI test result will be contacted (using a prior agreed pseudonym) and will be treated by the study team and partner notification using client referral undertaken.

***dd. 9.2 Safety issues***

As the transmission of HIV and other blood-borne pathogens can occur through contact with contaminated needles, blood, and blood products, appropriate blood and secretion precautions will be employed by all personnel in the drawing of blood and shipping and handling of all specimens for this study. Staff training will be given to all employees given regarding universal precautions and avoidance of needle-stick injuries. A policy for needle-stick injuries is in place. All staff will be vaccinated against Hepatitis B and encouraged to have COVID19 vaccination. Residual specimens, used specimen containers and laboratory waste will be placed in sealed autoclaved bags, autoclaved, and incinerated at the end of each working day. COVID19 Infection prevention and control procedures will be in place including use of masks, hand sanitisers and social distancing practised by staff, clients and participants.

- **10. Administrative Procedures**

***ee. 10.1 Regulatory approvals***

The trial will be conducted in accordance with the principles of the Declaration of Helsinki and in full conformity with relevant regulations and with the ICH Guidelines for Good Clinical Practice (CPMP/ICH/135/95) June 1996. Prior to implementation of this protocol, and any subsequent full version amendments, the protocol and the consent form(s) will be approved by the MRCZ, the LSHTM Ethics Committee and the BRTI IRB. The PI will register as a foreign researcher with the RCZ.

***ff. 10.2 Trial registration***

The trial has been registered with Clinicaltrials.gov Registry (<https://clinicaltrials.gov/>): Trial number NCT 03719521

***gg. 10.3 Indemnity***

LSHTM holds Public Liability ("negligent harm") and Clinical Trial ("non-negligent harm") insurance policies which apply to this trial.

***hh. 10.4 Study monitoring***

The MRCZ will conduct regulatory inspections to ensure that study procedures are compliant with GCP and will assess adherence to protocol and to SOPs, and confirm the quality and accuracy of information being collected. The study may also be subject to an audit by the RGIO office at LSHTM under its remit as the Trial Sponsor. External trial monitoring will be carried out by the Research Support Centre at the University of Zimbabwe. The study team will allow the study monitors to inspect study facilities and documentation, as well as to observe the performance of study procedures. An independent TSC will oversee trial progress, regularly review relevant information from other sources (e.g. other related trials) and advise the study team.

***ii. 10.5 Protocol compliance***

The study will be conducted in full compliance with the protocol. The protocol will not be amended without prior written approval by the PI. All protocol amendments will be submitted to and approved by the MRCZ, the LSHTM Ethics Committee and to the BRTI IRB prior to implementing the amendment. At the end of the study the MRCZ will be notified of the completion of the study (using the FORM 105- study termination form) and a final study report will be sent to the MRCZ.

***jj. 10.6 Maintenance of records***

The study team will maintain and securely store complete, accurate and current records throughout the study. All study records will be maintained for five years after the end of the study, as per MRCZ regulations. Study records include

protocol registration documents, all reports and correspondence relating to the study and documentation related to study participants (including informed consent forms, locator forms, case report forms, notations of all contacts with the participant, and all other source documents).

**kk.**

## ***ll. 10.7 Use of data and publications***

All processes related to data use will follow the principles of Good Clinical Practice. At the time of publication of research the subset of data required for the purposes of verifying research findings will be made available for sharing, and will be placed in the institutional research data repository established by the LSHTM Research Data Management Support Service. This repository will enable direct download of records with codebooks to enable replication of the data analyses. A more complete sharing of data with any research group requesting access to individual data records will be done 12 months after completion of the study. At this point, all data and study tools will be made available through the LSHTM Institutional Research Data Repository. Data for sharing will be anonymised prior to release for data sharing. In addition, annotated questionnaires and STATA do-files used for data cleaning and analysis will be available. All databases will be password-protected and accessible to authorised personnel only. The LSHTM open access repository will also enable access to repository contents through a searchable index. Where individual data are concerned, the informed consent procedure will clarify the possibility of use of anonymised data by other researchers. Data users will be required to acknowledge the source of data and to ensure that the regulatory requirements of the MRCZ and other ethical bodies reviewing the projects are met.

Publication of the results of this study will be governed by the requirements of the Wellcome Trust open access policy. All publications will be made available through PubMed Central (PMC) and Europe PMC as soon as possible and within six months of the journal publisher's official date of final publication. Where possible (and when an open access fee is paid), research papers will be licenced a Creative Commons Attribution licence (CC-BY).

